### Reimbursements

Participants will not receive payment, although complementary reusable water bottles and gym tops will be provided.

In Part A of the study, participants who were discharged from the inpatient setting over the course of the trial were invited to return to the hospital to resume HIIT sessions, subject to COVID-19 social restrictions, and associated travel costs were reimbursed. In Part B of the study, participants who are discharged from the inpatient setting will not be invited to the hospital to resume HIIT sessions due to insurance limitations, COVID-19 social restrictions and simplistic nature of the study.

### Follow-up

Participants who took in part A of the pilot study were invited to take part in individual semi-structured follow-up qualitative interviews. We hoped to conduct each qualitative interview within 3 weeks of each participant finishing the HIIT pilot study/ within 3 weeks of drop-out. We aim to find out (1) how participants experienced the intervention, (2) if there are any parts of the intervention that could be improved and (3) what factors influenced people in completing/not completing the intervention.

Qualitative interviews took place via telephone or video call. Each qualitative interview begun with the issuing of consent forms. Then, a series of simple questions about the positive aspects and weaknesses of the intervention were asked, and participants answered verbally. Overall, each individual interview was scheduled to take 30–60 min.

Material gained from the follow-up will be analysed using thematic analysis [82]. The themes generated will address the barriers and facilitators and perceived enjoyment of the HIIT intervention and areas for improvement for future work. As such data generated will seek to complement the acceptability and feasibility data gathered from the primary trial endpoints. We sought to offer an interview to all patients recruited to Part A of the study.

### Criteria to indicate that a future effectiveness trial is feasible

At present, no large-scale study is planned; however, feasibility outcomes will provide an indication as to whether a future effectiveness trial is warranted [48]. Criteria that indicate that a future effectiveness trial is feasible include (1) a majority of wards agreeing to hosting the project, (2) meeting stated recruitment (40 participants to the RCT and 10 participants to the naturalistic study phase), (3) comparable completion rates and adherence to other exercise interventions carried out in people with SMI (drop-out rates of previous exercise interventions in people with SMI has averaged 24–32.5% and adherence to scheduled sessions has averaged 55–94% [41, 42, 83], (4) lack of serious exercise-related AEs and (5) participants expressing that the conduct of the intervention was acceptable.

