## Methods/design

### Design

This pilot study follows a two-part design as a result of COVID-19 and consequent social restrictions.A parallel non-blinded randomised controlled trial (RCT) of HIIT compared to treatment as usual (TAU). Recruitment commenced in January 2020 and was suspended in March 2020 in accordance with COVID-19 social restrictions and corresponding Health Research Authority (HRA) guidelines. Participants randomised to HIIT were allocated to 12 weeks of HIIT twice weekly, delivered in a face-to-face setting. Participants assigned to TAU were instructed to maintain their usual dietary habits, and no restrictions were applied to their current level of physical activity.The study design was then adapted to a COVID-19 compliant naturalistic study of HIIT uptake in inpatient psychiatric settings. All eligible participants will be invited to take part in two sessions of HIIT per week, delivered by the research team remotely or in person depending on COVID-19 social restrictions. Additionally, patients will be able to use the bike to conduct self-directed sessions of their own chosen length and intensity. No time limit for participation will be applied. Recruitment to the naturalistic study design began in May 2021 and is ongoing.

The novel two-part design is based on the need to adapt to COVID-19 restrictions. The pilot design (Part A) is registered online (ClinicalTrials.gov Identifier: NCT03959735) and has been reported in accordance with the CONSORT for reporting of pilot and feasibility trials [48], and the SPIRIT guideline for main trials was consulted [49]. Ethical approval was obtained from London Bloomsbury Ethics Committee (IRAS ID: 263996, REC reference 19/LO/0901) for part A of the research and governance approval was granted from local National Health Service (NHS) bodies for part B of the research (Lewisham and Croydon NHS governance teams). A flow diagram of the study design is provided in Figs. 1 and 2, and the schedule of enrolment, interventions and assessments is provided in Fig. 3.

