**Fig. 3 Fig3:**
[figure not shown]
Schedule of enrolment, interventions and assessments in RCT

The RCT element of the study was suspended and then adapted due to the COVID-19 pandemic and the pausing of research projects. The naturalistic study is currently being undertaken to address issues surrounding the small sample size following the early termination of the RCT. There are currently no plans to resume recruitment in the RCT capacity. Specifically, a naturalistic design is being undertaken, rather than continuing with the original RCT format, due to the suspected difficulties in recruiting enough participants to fulfil both HIIT and TAU arms in the RCT design during covid. New admissions to inpatient wards dropped during the first wave of the pandemic, with an additional 2441 patients discharged from the hospital setting to free up bed capacity for the emergency response and to reduce the risk of infection [50]. This means that there were fewer inpatients with SMI overall, with many of those remaining in inpatient settings experiencing a greater symptom load, a more negative impact on functioning with attendant reduced likelihood and capacity of consenting to research and completing research assessments. The adapted naturalistic design will allow for the collection of feasibility and acceptability data which are the primary outcomes of the pilot study. Moreover, those who are more severely ill are less likely to participate in RCTs of lifestyle interventions [51]; thus, the use of a naturalistic design may provide a greater indication of uptake of HIIT in a clinical capacity.

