### Participants

Participants are being recruited from adult inpatient settings operating in SLaM, through adverts and presentations at ward-based community meetings for patients and via clinician referral. Additionally, posters are being displayed onwards with a request that anyone with an interest in taking part should contact the research team. All those who display an interest will be given written information on the study and invited to take part, providing they meet study eligibility criteria.

Individuals are eligible for the study if they meet the following criteria: (1) a service user receiving inpatient care in the participating NHS Trust for a severe mental health condition (including schizophrenia, MDD and bipolar disorder), (2) sufficient command of spoken English, and (3) able to provide written informed consent. Exclusion criteria include (1) a medical condition that impedes exercise (e.g., chronic back pain), (2) an eating disorder (e.g., anorexia nervosa, bulimia nervosa) characterised by excessive exercise, and (3) pregnancy. Additionally, in Part A of the research design eligibility was limited to those aged 18–60 years old.

We aimed to recruit 40 participants to the RCT phase, 20 in the intervention and 20 in the control group over a 1-year period. This number is based on recruiting a big-enough sample to assess the feasibility of the study and on the resources available [52]. We aim to recruit 10 participants to the naturalistic phase of the study. This reduced sample considers COVID-19-related challenges to recruitment, including reduced referrals and admissions to inpatient mental health wards during the pandemic [50].

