#### RCT design: Part A

Participants completed a sociodemographic questionnaire, mental health assessments, a cognitive test, anthropometric measures, lifestyle assessments and the bicycle YMCA submaximal fitness test [54]. The YMCA fitness test predicts the maximum rate of oxygen consumption (VO2max) during incremental exercise via measuring heart rate changes in response to an increase in resistance. It is an extrapolation method whereby heart rate workload points are gathered and extrapolated to age-predicted maximal heart rate [54]. Mental health assessments, the cognitive test, anthropometric measures, lifestyle assessments and the bicycle YMCA submaximal fitness test were to be repeated at week 6 and week 12 (post-intervention). Participants who were not physically able to complete the YMCA test were excluded from the study due to low baseline fitness and suspected difficulties in exercising at high intensity, this decision was undertaken to minimise the potential occurrence of AEs. Following successful completion of these assessments, the participant was assigned a unique code that was sent to King’s Clinical Trial Unit for randomisation. Participants were randomised in a 1:1 ratio to HIIT or TAU conditions using block randomisation with varying block sizes. Participants and researchers were notified of allocation after completion of all baseline assessments.

Those randomly allocated to the HIIT arm received two, one-to-one, sessions per week for 12 weeks, comprising 24 sessions in total in addition to TAU. HIIT sessions took place in the hospital physiotherapy department and were supervised by a member of the research team, and additional support was provided by a healthcare assistant, nurse or occupational therapist where Section 17 leave conditions stipulated accompany off ward by ward-based staff (Mental Health Act, 1983, [55]).

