### Data analysis

Acceptability and feasibility outcomes will be reported post-randomisation and summarised by treatment arm (HIIT and TAU) and study phase (RCT and naturalistic phase). Descriptive statistics including percentages and raw figures will be used to assess feasibility outcomes and acceptability survey responses. All AEs will be listed. Satisfaction scores (a measure of acceptability) will be collated to form a mean satisfaction rating.

Data analysis, for secondary and tertiary measures, will be simplified to account for small sample size owing to suspension of the RCT in line with COVID-19-inflicted restrictions. Data analysis plan suggested a formal statistical analysis whereby secondary outcome variables measured at the intervention time points (6 and 12 weeks) were to feature as dependent variables with, treatment arm (HIIT or TAU), time (6 or 12 weeks), baseline BPRS, baseline fitness and baseline anthropometric measurements included as covariates.

In lieu of the above plan, to evaluate effectiveness of the intervention in line with our secondary aim, changes pre- and post-intervention in mental and physical parameters will be assessed, and Cohen’s *d* and confidence intervals will be calculated to determine between-group effect size for mean change. This secondary analysis will be based on the intention-to-treat sample.

Similarly, for the tertiary outcomes, changes pre- and post-intervention in psychological wellbeing, psychological distress, fatigue and appetite and cigarette cravings following a single bout of HIIT will be assessed, and Cohen’s *d* and confidence intervals will be calculated to determine between-group effect size for mean change. As above, this analysis will be based on the intention-to-treat sample. An additional analysis will be conducted with those participants who adhered to the HIIT protocol (completed the full 19-min HIIT session and who reached the target heart rate).

Data analysis will be conducted using Statistical Package for the Social Sciences (SPSS) version 27 (Chicago, IL, USA).

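### Feasibility criterion 2 still asks for 40 RCT participants although the RCT closed after at most about three months, so its RCT half is already failed and measures the suspension rather than recruitability

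*Protocol article*

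**What the plan says.** The section on criteria for a future effectiveness trial lists five items. The second is "meeting stated recruitment (40 participants to the RCT and 10 participants to the naturalistic study phase". The two targets are joined by 'and'.

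The RCT target comes from the Participants section: "We aimed to recruit 40 participants to the RCT phase, 20 in the intervention and 20 in the control group over a 1-year period". Its basis is stated there too: "This number is based on recruiting a big-enough sample to assess the feasibility of the study and on the resources available".

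The Design section reports what happened to that plan: "Recruitment commenced in January 2020 and was suspended in March 2020". The text after Fig. 3 adds "There are currently no plans to resume recruitment in the RCT capacity" and explains the second phase: "The naturalistic study is currently being undertaken to address issues surrounding the small sample size following the early termination of the RCT". The number actually recruited to the RCT is not given.

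The naturalistic target is 10 in the Participants section and in criterion 2, but 6–8 in the Abstract.

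**The concern.** Recruitment numbers are one of the primary feasibility endpoints (Primary outcomes, item b). The RCT half of criterion 2 is the only benchmark the article gives for recruitment into a randomised comparison. A benchmark is useful if good recruitment would meet it and poor recruitment would miss it. Here accrual stopped for an outside reason after at most a quarter of the planned period, so a service that recruited exactly on plan and one that recruited badly both miss 40. The criterion cannot tell them apart.

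This does not look like text left over from before the pandemic. The same criterion names the naturalistic target of 10, so it was written or revised when the closure of the RCT was known. Other parts of the article were adapted: the Data analysis section replaces the planned secondary analysis because of the small sample, and the Participants section puts the target of 40 in the past tense.

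At stake is how the pilot's recruitment result is read. If the miss is counted, it counts against feasibility for a reason unrelated to patients. If it is discounted, nothing written in advance says on what basis.

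**Working it through.** **Inputs from the article**
- RCT target: 40, as 20 + 20, over 1 year (Participants).
- RCT recruitment opened in January 2020 and was suspended in March 2020 (Design). Exact days are not given.
- No plan to resume (Design, text after Fig. 3).

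**The plan's own figure.** 20 + 20 = 40, which agrees with criterion 2. The target rests on feasibility and resources, so there is no power calculation to reproduce.

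**Planned rate.** 40 / 12 = 3.33 per month, or 40 / 366 = 0.109 per day (2020 was a leap year).

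**Open window.** The shortest reading is 31 January to 1 March 2020, about 30 days. The longest is 1 January to 31 March 2020, 31 + 29 + 31 = 91 days.

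**Expected recruits if accrual ran exactly on plan**

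| Days open | Expected = 40 × days / 366 | Share of 40 | Multiple of planned rate needed to reach 40 |
|---|---|---|---|
| 30 | 3.3 | 8% | 366 / 30 = 12.2 |
| 61 | 6.7 | 17% | 366 / 61 = 6.0 |
| 91 | 9.9 | 25% | 366 / 91 = 4.0 |

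Taking recruitment as a Poisson count at the planned rate, the chance of 40 or more is below 1 in 10^11 even with the longest window.

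**Would a pass mark of 3.3 per month repair the criterion?** Under the same Poisson assumption, a trial whose true rate equals the plan reaches the mark about half the time:
- two months open, expected 6.7, at least 7 needed: P = 0.50;
- three months open, expected 10.0, at least 10 needed: P = 0.54.

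A bare cut-off would therefore fail an on-plan trial about as often as not.

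**How precise could an observed rate be?** Suppose, for illustration, 10 recruits in 91 days. The exact 95% Poisson interval for the count is 4.8 to 18.4. With 91 / 30.5 = 2.98 months open, that is 1.6 to 6.2 per month around an estimate of 3.4. The interval is wide, but it says something about recruitment, which the comparison with 40 does not.

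**The other half of criterion 2.** Reaching 6, 7 or 8 naturalistic participants would meet the Abstract's aim and still miss the 10 that the criterion requires.

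**The case against.** The article is open about the suspension and its consequences, and keeping the pre-pandemic target in view with the reason for the shortfall is a defensible way to report. That is fair as to disclosure. It does not explain why the figure stands as a criterion to be met in a section that was written or revised for the two-part design.

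A reader might infer more: that the feasibility verdict as a whole is fixed as a failure. The documents do not support this. The criteria section says that its criteria include the five items, that the outcomes give an indication, and that no large-scale study is planned at present. It sets no go/no-go rule and does not require all five to be met. The other four criteria and the naturalistic half of criterion 2 remain open.

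A reader might also take the Data analysis wording, "Acceptability and feasibility outcomes will be reported post-randomisation", to mean that people lost before randomisation would vanish from the account, given that "Participants who were not physically able to complete the YMCA test were excluded from the study due to low baseline fitness". That over-reads a loose phrase. The primary endpoints include ward agreement and reasons for disinterest, which arise before randomisation. The same sentence also covers the naturalistic phase, which has no randomisation, so the phrase cannot work there as a filter. Nothing says these exclusions will go unreported.

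The last objection concerns the remedy. RCT accrual ended in March 2020 and the article appeared in November 2021, so any new benchmark is chosen when the count could already be known. This stands. Deriving the rate from the old target limits the freedom of choice but does not make the change prespecified.

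**Conclusion.** The concern holds for the RCT half of criterion 2. As written, it was already failed at publication, and the failure carries no information on whether this population can be recruited. On-plan accrual would have given about 3 to 10 of the 40. This range assumes uniform accrual at the planned rate with no start-up period, and any dates within the stated months. A slower start would lower it further. Because the actual RCT count is not given, the range is a projection and not an observed result; the article itself confirms that the sample was small.

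The overall feasibility judgement is not settled by this. The effect is limited to one criterion out of five, though that criterion supplies the only stated benchmark for recruitment to randomisation. The conflict between 6–8 and 10 affects the half of the criterion that was still recruiting.

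**What to change.** Restate the RCT half of criterion 2 for the adapted design:
- report the observed number recruited per month over the actual open window, using the real opening and suspension dates;
- give a confidence interval (exact Poisson would suit) and set it beside the originally planned 3.3 per month, without a bare pass/fail cut-off;
- label this as a change made after the suspension;
- state that missing the total of 40 does not count as evidence against feasibility.

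In the same criterion, settle on one naturalistic target and use it in the Abstract, the Participants section and the criteria section.

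The cost is wording only; no further data are needed beyond the dates and the count. The downside should be stated plainly: the benchmark is set after RCT accrual ended, and with so few expected participants the interval will be wide, so the result can only inform a judgement about recruitment and cannot decide it.

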### Patient and public involvement

The research design and participant facing documents were reviewed by a team with experience of mental health problems and their carers who have been specially trained to advise on research proposals and documentation through the Young Person’s Mental Health Advisory Group (YPMHAG) and the Feasibility and Acceptability Support Team for Researchers (FAST-R): two separate free, confidential services in England provided by the National Institute for Health Research Maudsley Biomedical Research Centre via King’s College London and South London and Maudsley NHS Foundation Trust. Moreover, an ex-service user was consulted in the design process and with knowledge in mental health disorders and exercise, both from personal experience and undergraduate study, was consulted in the design process.

Focus groups were conducted with inpatients with SMI, carers and clinical staff to investigate perspectives on implementing HIIT interventions for service users in inpatient settings, including perceived barriers and enablers (discussed in background section above) [47]. Practical and safety considerations were noted and methods to increase patient motivation were sought and incorporated into the research design.

## Discussion

This pilot study aims to evaluate the feasibility and acceptability of an exercise intervention for inpatients with SMI. To the best of our knowledge, no HIIT interventions have been developed and tested in the NHS. This study will allow us to understand the feasibility of deploying the HIIT intervention itself and the use of the primary, secondary and tertiary outcome measures. Upon completion of the study, we will have a detailed overview of whether the delivery and planned evaluation approach are feasible and acceptable to deliver as part of a multi-centre large-scale definitive trial; namely whether participants agree to take part, continue to attend HIIT sessions and assessments and adhere to the HIIT protocol. The design of the study, with both RCT and naturalistic study design elements, will allow us to determine feasibility and acceptability of HIIT research when delivered in both research and clinical/naturalistic settings. Both phases of the study will address the feasibility and acceptability of delivering HIIT, while the RCT element will offer an indication to whether mental and physical health measures can be obtained providing an indication as to whether a large scale RCT of HIIT is the best design to determine its clinical effectiveness. With this said, the design of the study has various limitations. Suspension of the RCT study phase due to COVID-19 will limit power to detect changes in secondary and tertiary outcomes, and these outcomes will not be measured during the naturalistic study phase. Moreover, recruitment is limited to one NHS trust (although participants will be recruited from three sites), and reliability of measures of adherence to target heart rate will be limited in the naturalistic study phase due to inability to use chest straps for monitoring heart rate.

The physical health of people with SMI remains a high priority, and exercise has been identified as a modifiable lifestyle barrier that has the potential to reverse cardiovascular and cardiometabolic disease risk and reduce associated premature mortality. The National Institute for Health and Care Excellence (NICE) guidelines recommend that interventions be offered to support people with SMI to be more active [84]. HIIT is a time-efficient intervention that has yielded benefits for physical and mental health in other settings and populations [28]. If HIIT is found to be feasible and acceptable in inpatients with SMI, there would be scope for large-scale work and the potential implementation of this intervention in inpatient mental health facilities.

